### Study design and setting

We will include 74 TBI patients with epidural hemorrhage (EDH), subdural hemorrhage (SDH), and subarachnoid hemorrhage (SAH) as diagnosed according to computed tomography (CT) scan or magnetic resonance imaging (MRI) findings by the neurosurgeon. Patients will receive vitamin D (cholecalciferol) drop (100,000 IU) or 1000 IU identical control drop in a 1:1 ratio through random assignment method. Vitamin D drops are manufactured by Zahravi Company under good manufacturing practice (GMP). Each vial of vitamin D drop is produced to be dissolved completely in 1 ml of extra virgin olive oil (Familia Company), through a nasogastric tube (NGT) for 5 days in TBI patients. Both high-dose and low-dose drops will have the same bottle, flavor, and aroma to the blinded.

### Sample size

To calculate the sample size, in accordance with a previous study [7], interleukin 6 (IL-6) will be used as the main variable and the type 1 error is considered with an alpha of 0.05. We estimated 62 TBI patients with 80% power to detect an effect size of 0.5 for reduction of IL-6 between the intervention and control groups as calculated with the formula shown below. Considering 20% dropouts in this study, the total sample size is estimated to be 37 participants in each group as calculated in the below formula [7]:
$$ \frac{\left(Z1-\frac{\alpha }{2}+Z1-\beta \right)2\ \left(\delta 12+\delta 22\right)}{\left(\upmu 1-\upmu 2\right)2} $$

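### The 62 patients match the formula's per-group answer but are used as the trial total, so power for an effect of 0.5 SD is about 49% (range 47% to 56%), not 80%

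*Protocol article*

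**What the plan says.** All the inputs are in the Sample size section of the protocol article. IL-6 is the variable used for sizing. On error rate the text says "the type 1 error is considered with an alpha of 0.05", and the printed formula uses the normal quantile at 1 − alpha/2, so the test is two-sided. The claim is "We estimated 62 TBI patients with 80% power to detect an effect size of 0.5 for reduction of IL-6", as a difference between the two arms. The formula divides by the squared difference of the two means and carries the sum of the two group variances. No IL-6 means or standard deviations are given.

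The next sentence reads: "Considering 20% dropouts in this study, the total sample size is estimated to be 37 participants in each group". The Study design and setting section confirms the total, "We will include 74 TBI patients with epidural hemorrhage (EDH), subdural hemorrhage (SDH), and subarachnoid hemorrhage (SAH"), with 1:1 allocation. The Proposed analysis section names an independent t-test or a Mann-Whitney test for continuous variables.

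**The concern.** The formula gives the size of one group. A result of about 62 from it means 62 in each arm, yet the trial has 37 in each arm after the dropout allowance. The inputs, the formula and the enrolled number cannot all be right together.

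IL-6 is both the sizing variable and one of the primary inflammatory markers (Primary efficacy endpoint section). A reader who trusts the 80% would take a null IL-6 result as fair evidence against an effect of 0.5 SD. In fact the trial would miss such an effect about half the time. The Discussion presents this trial as groundwork for a larger multicentre study, so a false negative could end that line of work for the wrong reason.

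**Working it through.** **Inputs** (Sample size section unless noted): alpha 0.05 two-sided, z = 1.960; power 80%, z = 0.8416; effect size d = 0.5, read as a standardised mean difference with equal standard deviations; dropout 20%; 74 enrolled, 1:1 (Study design and setting).

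**1. Reproducing the 62.** With equal standard deviations the printed formula becomes

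n per group = 2 × (1.960 + 0.8416)² / 0.5² = 62.79.

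With z rounded to 1.96 and 0.84 it is 2 × 2.80² / 0.25 = 62.72. Truncated, either gives 62. So 62 is recovered as a per-group number. As a total it is not: the total is 2 × 63 = 126, or 128 with the t-based figure of 64 per group (63.8 before rounding).

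**2. How the 62 was used.** 62 × 1.2 = 74.4, taken as 74, and 74/2 = 37 per group. Equivalently, 31 × 1.2 = 37.2. The plan therefore treated 62 as both arms combined, 31 per arm.

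**3. Power at d = 0.5, two-sided alpha 0.05.** Normal approximation: power = Φ(d × √(n/2) − 1.960). For n = 31 this is Φ(0.5 × √15.5 − 1.960) = Φ(0.0085) = 50.3%. The t-test values use the noncentral t distribution.

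| Evaluable per group | Normal | t-test |
|---|---|---|
| 29.6 (74 × 0.8 = 59.2 in total) | 48.5% | 47% |
| 31 (the plan's 62 in total) | 50.3% | 49.1% |
| 37 (all 74, no loss) | 57.6% | 56.4% |
| 63 | 80.1% | 79.5% |
| 64 | not run | 80.1% |

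**4. Effect detectable with 80% power (t-test).** d = 0.72 with 31 per group, 0.74 with 59 evaluable in total, and 0.66 with 37 per group.

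**5. Number needed for the stated claim.** 126/0.8 = 157.5 and 128/0.8 = 160, so about 158 to 160 randomised with 20% loss.

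**6. The dropout step.** To keep 62 after losing 20%, 62/0.8 = 77.5, so 78 must be enrolled. Multiplying by 1.2 gives 74, and 74 × 0.8 = 59.2 falls short of the plan's own 62. This costs about 2 points of power (49% to 47%), which is small beside the halving.

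**7. Other routes to 62.**
- One-sided alpha contradicts the printed formula and needs 50 per group, 100 in total. With 31 per group its power is still only about 62%.
- Cohen's f = 0.5 needs about 33 to 34 patients in total, which is not 62.
- A one-sample formula gives 31.4, which would explain 31 per group. It is not the printed formula and does not suit a comparison of two groups, so the shortfall would be the same.

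**The case against.** Four points can be made for the plan.

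**The effect size may not be standardised.** The section gives no means or standard deviations and refers to an earlier study. If 0.5 were a raw difference, a standard deviation of about 0.70 would make 31 per group sufficient, since 62.79 × 0.70² ≈ 31. Nothing in the text supports this reading. The term effect size normally means a standardised difference, and the near-exact match with 62.8 points the same way. It stands only as an assumption to be stated.

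**The cause is inferred.** The protocol does not say that a per-group figure was taken as a total, and 62.8 would normally be rounded up to 63. That is fair, but the power shortfall depends only on the enrolled number, whatever produced the 62.

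**The figure of 49% is one of several.** The Proposed analysis section specifies intention to treat, so power could reach 56% if all 74 patients supply IL-6 data. That stands, and the range should be given. Some loss is likely, however: IL-6 is measured on days 7 and 14, and the Exclusion criteria list death before 7 days.

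**Adjustment could recover power.** With 31 per group, a baseline correlation of √(1 − 31/62.79) ≈ 0.71 would restore 80%; with 37 per group, √(1 − 37/62.79) ≈ 0.64. The protocol states no such correlation and its formula has no such term. The covariates named for the primary endpoint are age, sex, type and severity of injury, not baseline IL-6.

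It is also true that the document does not say how a null result would be read. The defect is the false power statement itself, and the misreading is its foreseeable consequence.

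**Conclusion.** The concern holds. By the protocol's own formula and inputs, 62 is the requirement for one group, and the trial has 37 per group before any loss. Power for 0.5 SD is 47% to 56% depending on loss, 49% at the plan's own 31 per group. That is some 24 to 33 percentage points below the stated 80%. The number enrolled supports 80% power only for effects of about 0.66 SD (no loss) to 0.74 SD (20% loss).

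This rests on reading 0.5 as a standardised difference with equal standard deviations, a two-sided test as printed, and an unadjusted comparison of two groups. The dropout arithmetic is a separate and minor error in the same direction.

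**What to change.** Keep the 74 patients; the Trial status section reports recruitment as completed. Correct the Sample size section as follows.

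- State that the formula's result is per group and that 0.5 is a standardised difference.
- Replace the power claim with wording such as: 74 randomised, about 59 evaluable (about 30 per group) after 20% loss; 80% power for a standardised IL-6 difference of about 0.74, and about 47% power for 0.5.
- Compute the dropout allowance as n/(1 − 0.20).
- Present the IL-6 result as an estimate with a 95% confidence interval, and say that a null result will not be taken to rule out a difference of 0.5 SD.

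The cost is wording only. No patients or procedures are added, but the detectable effect has to be stated as less favourable than it now appears.

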## Background

Vitamin D is an essential hormone for calcium homeostasis and its intestinal absorption. It also has an important role in several neuromuscular activities and metabolic responses [1]. Recent studies indicated that the active form of vitamin D (calcitriol) may have a crucial function in modulating immune responses to inflammatory conditions and infectious diseases [2, 3]. According to previous data, vitamin D deficiency has been associated with a high incidence of adverse events and mortality in critically ill patients [4]. Vitamin D can induce production of anti-inflammatory cytokines and some antimicrobial proteins such as cathelicidin by macrophages and neutrophils [3]. Antimicrobial proteins are expressed significantly in the respiratory epithelium and other organs, and they could reduce risk of infections in integumentary barrier sites [5, 6]. Notably, infectious diseases such as pneumonia and sepsis are common in traumatic patients leading to more than 20% rate of death in these patients; in addition, there is a high prevalence of vitamin D deficiency in these patients; therefore, vitamin D treatment is of high importance in traumatic brain injury (TBI) patients [7–9]. Moreover, vitamin D deficiency is also related to serious complications such as coma, slow neurological recovery, and critical illness polyneuropathy in TBI patients [10, 11]. Although there has been a direct association between vitamin D deficiency and adverse clinical outcomes in critically ill patients, the data regarding vitamin D supplementation from randomized clinical trials are limited [12]. In addition, vitamin D supplementation has not been shown whether it efficiently affects the endpoints of TBI patients or not [4, 9]. The type of vitamin D supplement, route of intervention, and speed of normalization may be associated with clinical outcomes in critically ill patients [4, 9, 12]. As compared to vitamin D injection, enteral vitamin D administration seems to be more effective and is considered safe [13, 14]. To date, studies on the effects of vitamin D on TBI patients have been inadequate and could not provide definitive conclusions [15–17]. The purpose of the present study is to determine the effect of high-dose vitamin D (cholecalciferol) supplementation versus low dose on mortality rate and inflammatory cytokine levels, in critically ill TBI patients under enteral nutrition therapy at intensive care unit (ICU).

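### The 20% dropout allowance was applied as 62 × 1.2 instead of 62 / 0.8, so 74 patients cover only 16% loss and leave about 59, not 62, at the stated rate

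*Protocol article*

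**What the plan says.** The Sample size section names IL-6 as the sizing variable and states that "the type 1 error is considered with an alpha of 0.05"; its formula uses α/2, so the test is two-sided. It continues: "We estimated 62 TBI patients with 80% power to detect an effect size of 0.5". The allowance follows: "Considering 20% dropouts in this study, the total sample size is estimated to be 37 participants in each group". Study design and setting confirms the total ("We will include 74 TBI patients") and the allocation ("in a 1:1 ratio through random assignment method").

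Four other places bear on how much loss to expect:

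- Exclusion criteria, listed apart from the non-entry criteria, takes out patients who die before day 7, whose family asks to stop, who receive a different medication protocol, or who meet any of the first five non-entry items.
- Study assessments places IL-6 sampling at baseline, day 7 and day 14.
- Proposed analysis states intention to treat.
- Background remarks that "infectious diseases such as pneumonia and sepsis are common in traumatic patients leading to more than 20% rate of death in these patients".

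**The concern.** A dropout allowance should ensure that the number needed for the power claim remains after the stated loss. Here it does not: 20% of 74 is more than the 12 patients added to 62. The stated power therefore belongs to a number of patients that the plan's own loss rate does not leave.

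The content of the allowance is also undefined. Deaths before day 7 and several in-ICU events lead to removal, and each may cost follow-up IL-6 values, yet the article does not say whether these are counted in the 20%. Removing randomised patients also conflicts with the stated intention-to-treat analysis and discards samples that could be used. At stake are an accurate statement of what 74 patients can deliver and a consistent definition of who is analysed.

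**Working it through.** **Inputs.** From Sample size: two-sided α = 0.05, power 80%, 62 patients before the allowance, effect size 0.5, loss 20%, 37 per group. From Study design and setting: 74 in total, 1:1 allocation, so 62 means 31 per group.

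**1. Reproducing the printed figure.** With n × (1 + d): 31 × 1.2 = 37.2 and 62 × 1.2 = 74.4. These round to the printed 37 and 74, so the figure does reproduce, by the multiplicative shortcut.

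**2. The correct inflation.** With n / (1 − d): 31 / 0.8 = 38.75, so 39 per group and 78 in total (62 / 0.8 = 77.5). The shortfall is 2 per group, 4 in total.

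**3. What 74 delivers.** At 20% loss, 74 × 0.8 = 59.2, about 59 patients. The loss that still leaves 62 is (74 − 62) / 74 = 12 / 74 = 16.2%.

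**4. Power cost on the protocol's premise.** Suppose 31 per group do give 80% power. In the normal approximation this implies a standardised difference d = (1.960 + 0.842) × √(2/31) = 0.712. With 59.2 / 2 = 29.6 per group, power = Φ(0.712 × √(29.6/2) − 1.960) = Φ(0.778) = 78.2%. A t-test calculation gives d = 0.723 and 78.1%. Equivalently, the effect detectable with 80% power moves from 0.712 to (1.960 + 0.842) × √(2/29.6) = 0.728.

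**5. The premise itself.** The section prints neither means nor SDs, so I read 0.5 as a standardised difference (assumption). Then n per group = 2 × (1.960 + 0.842)² / 0.5² = 62.8, that is 63 per group, 126 in total. With 62 in total, power is Φ(0.5 × √(31/2) − 1.960) = 50.3%; with 59.2 it is 48.5%. On this reading, too, the allowance error costs about 2 points, but from a much lower start.

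**6. Chance of falling below 62.** This needs 13 or more losses among 74. The binomial probability for an assumed true loss rate is:

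| Assumed loss | P(13 or more lost) |
|---|---|
| 10% | 3% |
| 15% | 31% |
| 20% (the plan's rate) | 74% |
| 25% | 95% |

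Only the 20% row uses a rate from the document.

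**The case against.** The strongest reply is that the proven error is small: 2 patients per group and about 2 power points. Multiplying by 1.2 is a common shortcut, and if true loss is 10% or 15%, 62 patients would probably remain. All of this stands, and it limits the weight of the point. It does not make the stated figure right, because at the plan's own 20% the target is more likely missed than met.

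A reader might also infer that the Background death rate and the removal rules together push loss beyond 20%, so that 62 evaluable patients cannot be reached. The document does not support that:

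- The Background figure is a general remark about infection in trauma patients. It has no time window and is not offered as this trial's expected mortality, and the non-entry criteria bar patients with a history of infection, sepsis and several chronic diseases.
- Only deaths before day 7 are listed for removal. A patient who dies between days 7 and 14 can still give a day-7 IL-6 value, and a death after day 14 costs none.
- No rate is given for family withdrawal, medication change or meeting the non-entry items, and nothing says that these lie outside the 20%.

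Power figures for 30% or 40% loss would therefore rest on assumption alone.

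Finally, it may be said that the removal rules are a separate matter from dropout arithmetic. They are a separate cause, but they determine what loss means here and how many IL-6 values the 74 patients yield.

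**Conclusion.** The point holds as an arithmetic error in a stated design figure. The allowance was multiplied on instead of divided out, so 74 patients cover 16.2% loss and not 20%, and at 20% about 59 remain. The cost is about 2 percentage points of power (80% to 78%) if one accepts that 62 patients give 80%. That acceptance is doubtful: with 0.5 read as a standardised difference, 62 in total give about 50%, a far larger problem than the allowance.

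Whether loss exceeds 20% cannot be settled from the document. The article leaves open what the allowance includes and gives no expected loss at day 7 or day 14. What it does show is that the removals under Exclusion criteria, early deaths among them, are inconsistent with the intention-to-treat analysis under Proposed analysis.

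**What to change.** Trial status reports that recruitment is complete, so none of this asks for more patients.

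- In Sample size, state that 74 enrolled with 20% loss leave about 59 evaluable patients, or that 74 cover 16% loss.
- Say whether deaths and the removals under Exclusion criteria are counted in the allowance, preferably giving deaths before the IL-6 time point and other losses separately.
- Restate the power, or the detectable effect, at the resulting number, giving the assumed IL-6 mean difference and SDs so that the step from effect size to 62 can be checked.
- Reconcile Exclusion criteria with Proposed analysis: keep every randomised patient in the analysis with whatever IL-6 samples exist, subject to family withdrawal of consent. This concerns who is analysed, not when the supplement is stopped.

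The cost is revised wording, a clear definition of the analysis set and a less favourable power statement.

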### Randomization and blinding

Block randomization method will be considered for this trial study. TBI patients will be randomized (in four blocks) into the intervention group and control group based on a blinded randomization list generated and online databases for clinical trials (https://www.sealedenvelope.com) and will be managed by the research director of Clinical Nutrition Department, Mashhad University of Medical Sciences. Patients will be allocated by random according to the severity of brain injury (GCS 7–8 and 8–9), type of brain injury (EDH, SDH, and SAH), gender, and age to ensure match distribution of these factors in all four blocks. Given that the ICU supervisor has no knowledge of which vial contains high dose or low dose of vitamin D, TBI patients will be randomized to group A or B. The label A or B on vials will be deleted by the research director before allocating the study supplements; thus, the medication will appear similar to the study researcher and nurses. The TBI patient’s study identification code will be documented, and the intervention group may only be determined by comparing the patient’s study number to the reference blinded list, which only the research director will have access to until the trial is finished. Figure 2 indicates the SPIRIT schedule of evaluations and interventions.

### Proposed analysis

To determine the normal distribution of variables, the Kolmogorov-Smirnov test will be conducted. The analysis will be performed according to the intention-to-treat (ITT) test. We perfomed an independent t-test or the Mann-Whitney test for continuous variables and the chi-square or Fisher exact test for categorical variables. Repeated measure one-way analysis of variance (ANOVA) or multivariable covariance analysis (ANCOVA) will be conducted to examine differences in severity of brain injury score (GCS), APACHE II score, SOFA score, delirium score, and all variables at study baseline between the two groups. Kaplan-Meier test was conducted and compared with the use of the log-rank test for estimates of survival time. The *P* values less than 0.05 will be considered statistically significant.

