### Primary efficacy endpoint

The primary efficacy outcome for this trial will be assessed by comparing the changes in vitamin D levels and inflammatory markers (IL-6, monocyte chemoattractant protein-1 (MCP-1), and C-reactive protein (CRP)) between two groups. The rate of mortality in TBI patients until 28 days after admission (in ICU and regular ward) will be assessed in high- and low-dose vitamin D supplement groups. The impact of high dose versus low dose of vitamin D will be analyzed, with and without adjustment for age, sex, type of brain injury, and severity of injury. If the results differ after adjusting for the variables, the results of both analyses will be reported.

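### The primary marker analysis is not fixed to one version and leaves the measured baseline marker out of the covariates, and the one-way repeated-measures ANOVA, as named, cannot compare the arms

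*Protocol article*

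**What the plan says.** All references are to the protocol article.

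- **Normality and simple tests (Proposed analysis).** "To determine the normal distribution of variables, the Kolmogorov-Smirnov test will be conducted". For continuous outcomes, "We perfomed an independent t-test or the Mann-Whitney test for continuous variables".
- **Repeated measures (Proposed analysis).** "Repeated measure one-way analysis of variance (ANOVA) or multivariable covariance analysis (ANCOVA) will be conducted to examine differences" between the two groups in GCS, APACHE II, SOFA, delirium score and the baseline variables. The sentence names no covariates and no rule for choosing between the two methods.
- **Primary endpoint (Primary efficacy endpoint).** Changes in vitamin D, IL-6, MCP-1 and CRP are compared between the arms. The dose effect "will be analyzed, with and without adjustment for age, sex, type of brain injury, and severity of injury". Both results are to be reported if they differ. Secondary efficacy endpoints repeats the two-way adjustment.
- **Allocation (Randomization and blinding).** Allocation takes account of GCS severity, injury type, gender and age, which are the same four factors as in the adjustment list.
- **Measurements (Study assessments).** IL-6, MCP-1 and CRP are measured at baseline and on days 7 and 14.

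**The concern.** There are three linked weaknesses.

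1. **No single primary result.** A marker can be tested by t-test or Mann-Whitney, adjusted or unadjusted. A t-test estimates a difference in means, whereas Mann-Whitney addresses a shift in ranks. If the normality test decides between them, which the text implies but does not state, the data choose the effect measure. Because both versions are promised only when they disagree, the article does not say which one stands when they agree, or which one prevails when they do not.

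2. **Precision is given away.** The baseline marker value is likely to predict the follow-up value of the same marker, and it is already collected. The stated covariate list leaves it out. Subtracting baseline is not the same as adjusting for it, and it is less efficient than ANCOVA whenever the correlation is below 1.

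3. **A named method does not match its stated purpose.** A one-way repeated-measures ANOVA has time within patient as its only factor. It has no arm term and no arm-by-time term, so it answers whether scores change over time, not whether the arms differ.

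**Working it through.** **Inputs from Sample size and Study design and setting.** "the type 1 error is considered with an alpha of 0.05", which is two-sided because the printed formula uses the 1 − α/2 quantile; 80% power; effect size 0.5; 62 patients before dropout; 37 per arm after it; 1:1 allocation.

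**Assumed input.** The correlation r between baseline and follow-up marker is not given, so I take 0.3, 0.5 and 0.7.

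**Step 1: the plan's own figure.** n per arm = 2(1.96 + 0.842)² / 0.5² = 62.8, so 63 per arm or 126 in total. The stated 62 therefore fits as a per-arm number (power 0.795 at 62 per arm), not as a total. With 62 in total, or 31 per arm, power is Φ(0.5·√(31/2) − 1.96) = Φ(0.009) = 0.50 by the normal approximation, and 0.49 by the noncentral t. This shortfall is a separate matter. Here it only sets the starting point.

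**Step 2: variance with and without the baseline covariate.** With equal variances at both times, taking the follow-up SD as 1:

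- variance of the change score = 2(1 − r)
- residual variance with baseline as covariate = 1 − r²
- ratio = (1 − r²) / [2(1 − r)] = (1 + r)/2

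**Step 3: power when 0.5 is in change-score SD units** (noncentral t). Effective d = 0.5/√ratio.

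| r (assumed) | Ratio | Effective d | Power, 31 per arm | Power, 37 per arm |
|---|---|---|---|---|
| unadjusted change | 1 | 0.500 | 49% | 56% |
| 0.3 | 0.65 | 0.620 | 67% | 75% |
| 0.5 | 0.75 | 0.577 | 61% | 69% |
| 0.7 | 0.85 | 0.542 | 56% | 63% |

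At r = 0.5, 31 per arm has the precision of 31/0.75 = 41 per arm analysed as an unadjusted change.

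**Step 4: the other reading of the effect size.** If 0.5 is in follow-up SD units, power at 31 per arm (normal approximation) for r = 0.3, 0.5 and 0.7 is 38%, 50% and 72% for the unadjusted change, against 54%, 62% and 79% with the baseline covariate. The gain is in the same direction on both readings, and neither reaches 80% at 31 per arm.

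**Step 5: the ANOVA sentence.** The method in "Repeated measure one-way analysis of variance (ANOVA) or multivariable covariance analysis (ANCOVA) will be conducted to examine differences" is set against its stated aim, a difference between two groups. With one factor, that factor is either time, in which case arm is absent, or arm, in which case the design is not repeated-measures. A comparison of arms over time needs both factors and their interaction. The ANCOVA alternative can compare arms, but nothing says when it is used or with which covariates.

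**The case against.** The other side has several good points.

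- **The allocation factors are in the plan.** A reader of Proposed analysis alone might infer that the plan ignores them. It does not: Primary efficacy endpoint and Secondary efficacy endpoints both plan an adjusted version with the same four factors. What stands is that this version has no priority over the unadjusted one.
- **Baseline is used.** A reader might infer that baseline IL-6 is ignored. The outcome is a change, so baseline enters every comparison, and an unadjusted change score is unbiased under randomisation. The loss is precision, not validity.
- **ANCOVA is named.** The intended method may be a between-group repeated-measures model with the wrong label. That is plausible, but as written the label describes a method without an arm term. The sentence lists clinical scores and baseline variables, and does not name follow-up IL-6.
- **The normality step may cost little power.** A reader might infer that screening by Kolmogorov-Smirnov leaves skewed data to a weak t-test. The documents do not support that. The plan has a Mann-Whitney branch, which limits such a loss, and the article does not say whether critical values corrected for an estimated mean and SD are meant. What stands is that the effect measure is not fixed.
- **Loss of incomplete patients.** One might infer that only complete survivors would be analysed. The article states intention to treat, and handling of missing data may lie in an analysis plan that is not shown.

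Transformation and full model detail can also be left to that plan. The point here is narrower: the article does state a covariate list and a reporting rule, and both are poorly fixed.

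**Conclusion.** The concern holds in this limited form. The primary marker analysis is left open between two tests and between adjusted and unadjusted versions. The measured baseline marker is missing from the stated covariates. One named method cannot do what its sentence says.

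The size of the precision loss rests on an assumed correlation and on equal variances at baseline and follow-up. On those terms, adding baseline takes power at 31 per arm from 49% to between 56% and 67% for r from 0.7 to 0.3. The reference is the unadjusted change score. The plan's four-factor adjusted version may recover part of the gap if those factors predict the marker, and the documents give nothing to size that.

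It would be wrong to infer that baseline adjustment rescues the trial's power. It does not reach 80% at 31 per arm under any value shown, and the sample-size calculation needs its own correction.

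**What to change.** 1. Name one primary analysis for the markers: an ANCOVA, or a mixed model over days 7 and 14, of the log-transformed marker with arm, visit, arm-by-visit, baseline marker value, and severity, injury type, sex and age. State which visit gives the primary contrast, and report it as a ratio of geometric means with a 95% confidence interval.
2. Make that adjusted model primary. Report the unadjusted result as a sensitivity analysis in every case, not only when the two differ.
3. Replace the one-way repeated-measures ANOVA with the same type of model, containing arm and arm-by-visit and the baseline score, for GCS, SOFA, APACHE II and delirium score.
4. Do not let a normality test choose the effect measure. If Mann-Whitney is kept, label it a sensitivity analysis.

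The cost is wording only, since every covariate is already collected. Trial status reports that recruitment has ended, so the change should be dated before unblinding. If that is no longer possible, the revised analysis should be reported as specified afterwards.
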